# Oncologic outcomes of single-incision laparoscopic surgery versus conventional laparoscopic surgery for colorectal cancer (CSILS): study protocol for a multicentre, prospective, open-label, noninferiority, randomized controlled trial

**DOI:** 10.1186/s12885-022-09821-9

**Published:** 2022-07-07

**Keywords:** Study protocol, Colorectal cancer, Oncologic outcomes, Single-incision, Laparoscopic surgery, Randomized controlled trial

## Abstract

**Background:**

In most previous studies, single-incision laparoscopic surgery (SILS) for colorectal cancer (CRC) was feasible and safe in the short term. However, long-term oncologic outcomes remain uncertain, as only a few studies contained long-term survival data. SILS for CRC is still in the early stages of research. Further studies, particularly large-scale, prospective randomized controlled trials, are necessary to assess the value of SILS for CRC.

**Methods:**

This study is a prospective, multicentre, open-label, noninferiority, parallel-group randomized controlled trial that investigates the long-term oncologic outcomes of SILS compared to conventional laparoscopic surgery (CLS) for CRC. A total of 710 eligible patients will be randomly assigned to the SILS group or the CLS group at a 1:1 ratio using a central, dynamic, and stratified block randomization method. Patients with ages ranging from 18 to 85 years old, of both sexes, with CRC above the peritoneal reflection diagnosed as cT1-4aN0-2M0 and a tumour size no larger than 5 cm will be considered for the study. The primary endpoint is 3-year disease-free survival (DFS). The secondary endpoints include: intraoperative outcomes, postoperative recovery, postoperative pain assessment, pathological outcomes, early morbidity and mortality rate, cosmetic effects, quality of life, 3-year overall survival (OS), incidence of incisional hernia, 5-year DFS and 5-year OS. The first two follow-up visits will be scheduled at one month and three months postoperatively, then every three months for the first two years and every six months for the next three years.

**Discussion:**

Currently, no randomized controlled trials (RCTs) have been designed to investigate the long-term oncologic outcomes of SILS for CRC. This study is expected to provide clinical evidence of the oncologic outcomes of SILS compared to CLS for CRC to promote its widespread use.

**Trial registration:**

ClinicalTrials.gov: NCT 04527861 (registered on August 27, 2020).

## Background

### Rationale

Colorectal cancer (CRC) is a common malignant tumour of the digestive tract, and its global incidence ranks third among all malignancies [1]. Surgery is a major treatment for CRC. Laparoscopic surgery for CRC has been proven to be safe and effective compared with laparotomy by many randomized controlled trials [2–7], which provides many advantages, including less surgical trauma, better cosmetic results, and a shorter hospital stay [2–7].

Recently, with the extensive development of laparoscopic surgery and the extension of the concept of minimally invasive surgery, many institutions have begun studies on "scarless" surgery to reduce trauma and postoperative pain and improve the cosmetic effect. These studies mainly focused on natural orifice transluminal endoscopic surgery (NOTES) and single-incision laparoscopic surgery (SILS). The current clinical application of NOTES is greatly limited due to difficulties in ethics, gastrointestinal anastomosis, infection prevention, operation platforms, and instrument research [8, 9]. In contrast, SILS is attracting increasing attention. It is a way to transition to “scarless” surgery that is more feasible for generalized use in the future.

Single-incision surgery was reported as early as 1969, when Wheeless et al. [10] performed tubal ligation with laparoscopy through a single surgical channel. In 1997, Navarra et al. [11] first reported transumbilical single-incision cholecystectomy, performed through two 10-mm trocars set in a small transumbilical incision combined with suspension technology. Complete transumbilical cholecystectomy without any additional trocar was first performed by Podolsky et al. in 2007 [12], marking the development of SILS. CRC surgery is generally a semielective surgery. Radical resection is relatively complex and requires a higher degree of proficiency and precision. Therefore, it was not until 2008 that SILS was first reported for colorectal surgery. Bucher et al. [13] and Remzi et al. [14] independently performed right hemicolectomy for benign colonic polyps with good outcomes. In 2009, Bucher et al. [15] successfully performed single-incision laparoscopic radical left colectomy, being the first to apply SILS in malignant colorectal tumours.

Although the number of studies on this new method of surgery has increased year by year, the majority are retrospective studies with small sample sizes, and few are high-quality randomized controlled trials (RCTs). Although the feasibility and short-term safety of SILS were confirmed in most previous studies, the potential benefits are still controversial. Furthermore, the long-term oncologic outcomes remain uncertain, as only a few studies contained long-term survival data [16–18].

To the best of our knowledge, in addition to our single-centre RCT study [19], seven other RCT studies [18, 20–26], including three multicentre studies [18, 23, 25, 26] have been published on SILS for CRC. In the four earlier reported RCT studies [20–22, 24], the sample sizes were calculated inadequately, leading to less reliable conclusions. In addition, in Maggiori et al.’s multicentre study [25], the value of SILS for CRC could not be well assessed due to limited malignant cases. The SIMPLE trial [26] had the largest sample size and multicentre participation, making it the best-designed published RCT study to date. However, similar to Watanabe et al.’s study [18, 23], patients with cancers located in the rectum, descending colon, or transverse colon were excluded. No previous RCT studies were designed with long-term outcomes as the primary study endpoint.

Studies on SILS for CRC are still in the early stage. Therefore, further studies, particularly large-scale, prospective randomized controlled trials, are needed to assess its safety, efficacy, potential benefits, and long-term outcomes to evaluate its value in CRC.

### Objective and hypothesis

This study will investigate the long-term oncologic outcomes of SILS compared to CLS for CRC. The hypothesis is that the oncologic outcomes of SILS for CRC are noninferior to CLS.

## Methods/Design

### Settings

This CSILS study will be a prospective, multicentre, open-label, noninferiority, parallel-group randomized controlled trial. The trial will be conducted at 10 qualified clinical centres in China (Table 1). The CSILS protocol and this manuscript were prepared following the Standard Protocol Items: Recommendations for Interventional Trials (SPIRIT). This manuscript refers to version 1.1 of the full study protocol released on 6 February 2021.

**Table 1 Tab1:** Participating centers

Centers	Location
Ruijin Hospital, Shanghai Jiao Tong University School of Medicine	Shanghai
Dongfang Hospital Affiliated to Tongji University	Shanghai
Shanghai Cancer Center, Fudan University	Shanghai
RenJi Hospital, Shanghai Jiao Tong University School of Medicine	Shanghai
Changhai Hospital, Navy Medical University	Shanghai
Zhejiang Provincial People's Hospital, People's Hospital of Hangzhou Medical College	Hangzhou, Zhejiang
Shengjing Hospital, China Medical University	Shenyang, Liaoning
Liaoning Cancer Hospital & Institute	Shenyang, Liaoning
Shandong Provincial Hospital Affiliated to Shandong First Medical University	Jinan, Shandong
The General Hospital of Western Theater Command	Chendu, Sichuan

### Eligibility criteria

Patients between 18 and 85 years old, of both sexes, with cT1-4aN0-2M0 CRC diagnosed via computed tomography (CT) and/or colonoscopy according to the 8th Edition of the American Joint Committee on Cancer (AJCC) Cancer Staging Manual, with a tumour located above the peritoneal reflection and a tumour size no larger than 5 cm will be further screened for inclusion. Table 2 shows the detailed inclusion, exclusion, and withdrawal criteria.

**Table 2 Tab2:** Inclusion, exclusion, and withdrawal criteria

Inclusion criteria	Exclusion criteria	Withdrawal criteria
• 18 years < age < 85 years • Pathological colorectal adenocarcinoma • Tumor located in colon and rectum (the lower border of the tumor is above the peritoneal reflection) • Clinically diagnosed cT1-4aN0-2M0 lesions according to the 8th Edition of AJCC Cancer Staging Manual without preoperative neoadjuvant therapy performed • Tumor size of ≤ 5 cm • Performance status ECOG 0–1 • ASA class I to III • Informed consent	• BMI > 35 kg/m2 • Previous gastrointestinal surgery (except for appendicectomy) • Emergency operation due to complication caused by colorectal cancer (bleeding, perforation or obstruction) • Multiple malignant lesions • Familial adenomatous polyposis (FAP) or Inflammatory bowel disease (IBD) • Requirement of neoadjuvant therapy • Pregnancy or lactation • Severe mental disease • Severe liver and kidney dysfunction, coagulation dysfunction, or with serious comorbidities that cannot perform surgery • Requirement of simultaneous surgery for other disease • Other malignant disease history within 5 years	• Intraoperative or pathological confirmation of invasion of adjacent structures requiring combined organ resection or distant metastasis • Non-colorectal adenocarcinoma confirmed by postoperative pathology • Multiple malignant lesions confirmed by postoperative pathology • Requirement of emergency operation due to the change of illness state • Inability to undergo surgery or anesthesia due to the change of illness state • Receive treatment other than the protocol during the treatment period (except for treatment of tumor recurrence and metastasis) • Patient required to withdraw • Unable to complete the clinical trial due to various reasons • Treatment implemented is proven to violate the study protocol

*BMI* Body mass index, *ASA* The American Society of Anesthesiologists, *ECOG* Eastern Cooperative Oncology Group

Before participating in this study, surgeons will be required to pass a blinded evaluation of their surgical videos. They will be required to provide the CSILS study committee with 3 surgical videos of SILS and 3 of CLS for CRC performed within the last 6 months. The study committee will randomly select 2 surgical videos each and arrange a blind review with 3 peer experts. The surgeon will be permitted to join the study if the 3 reviewers unanimously approve the surgical technique and oncological outcomes shown in the videos.

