### Interventions

Preoperative nutritional support, bowel preparation, prophylactic systemic antibiotics, prophylactic anticoagulation, respiratory function training, and prophylaxis for other potential high-risk complications are administered according to the patient's condition and the routine of each study centre. Nasogastric tubes will not be routinely used.

Radical resection (R0) based on the same oncological principles is required for all operations. The principles include adequate surgical resection margins, complete or total mesocolic excision (CME/TME), and D3 lymph node dissection. Intraperitoneal operations must be performed using laparoscopic instruments supported by a camera system. In the SILS group, the operations will be performed through a single incision, usually with a transumbilical approach. A single port device and laparoscopic instruments will be placed through the small incision. In the CLS group, the operation will be performed with 3 to 5 trocars. Conventional laparoscopic instruments, precurved instruments, articulating instruments, 3D laparoscopes, and flexible laparoscopes, among others., may be used during the operation. Intestinal segment mobilization, lymph node dissection, and vascular ligation should be performed under laparoscopy. The specimen excision and the anastomosis will be allowed to be performed in an open state using an auxiliary small incision (usually the same size as the tumour). Auxiliary incisions will generally be limited to one, except in cases where a stoma is needed. According to the site of the tumour, appropriate surgical methods, including right colectomy, left colectomy, sigmoidectomy, and anterior resection, will be selected. Prophylactic ileostomy will be performed when necessary. Placement of drainage tubes will be decided by the surgeons. Unedited video recordings of the laparoscopic operations, photographs of the incisions, and photographs of the specimens will be documented.

The treatment strategy will be required to change (SILS to additional trocar/laparotomy; CLS to laparotomy) if one of the following happens: intractable intra-abdominal haemorrhage, severe organ damage, other serious or life-threatening complications related to surgical procedures or carbon dioxide pneumoperitoneum, or other technical or instrumental factors requiring conversions. When the length of the auxiliary incision is larger than 10 cm, conversion to laparotomy will be considered.

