### Sample size calculation

In this study, the 3-year DFS is the main effectiveness evaluation index for noninferiority evaluation. According to previous studies [27–29], the 3-year DFS of the CLS group was approximately 75%. This study assumes that the 3-year DFS of the study group is the same as that of the control group. The expected enrolment time is 3 years, and the follow-up time to reach the primary endpoint is 3 years. If the acceptable noninferiority limit of DFS in the three years of this study is 10%, when DFS is exponentially distributed, the corresponding HR limit is 1.49. This number will be combined with "Log-Rank Tests for Noninferiority" in the professional sample size estimation software NCSS-PASS (14th edition, NCSS, LLC, Utah, USA). When the unilateral statistical significance level is 0.025, the inspection efficiency is 80%, and the study group and the control group will be allocated in the ratio of 1:1, the required sample size of each group will be 284. Considering that the largest abscission rate in this clinical study is approximately 20%, it was finally determined that the sample size of each group will be 355 cases, and the total number of cases required will be 710.

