### Statistical methods

SAS 9.4 statistical software will be used to perform the statistical analyses. The noninferiority analysis for the primary endpoint of 3-year DFS will be conducted by comparing 95% confidence intervals of survival rates between the test and control groups on a modified intent-to-treat (MITT) population basis. Baseline data and validity analyses will be conducted on a modified intent-to-treat (MITT) basis. The primary endpoint will also be analysed on a per-protocol (PP) basis, with the MITT analysis results prevailing. Safety evaluation, including laboratory test data, will be conducted in the safety analysis population (SAP). There is no planned interim analysis for the 3-year DFS rate. Continuous data will be described as the means with standard deviations or medians with interquartile ranges, and categorical data will be expressed as frequencies and percentages. Comparisons between groups will be conducted using the Wilcoxon rank-sum test, Student’s t test, Pearson χ2 test, and Fisher exact test, as appropriate. Survival data will be analysed using the Kaplan–Meier method and log-rank test. A general linear model for quantitative indicators, logistic regression for qualitative indicators, and Cox's proportional hazards model for survival data will be used to assess the effects of baseline, treatment, centre, and treatment-by-centre interactions. A two-sided *p* value < 0.05 will be considered statistically significant.

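### Table 2 withdraws randomised patients on post-randomisation grounds that may depend on the operation, and nothing printed keeps them in follow-up or in the primary analysis

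*Protocol article*

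**What the plan says.** Table 2 (Eligibility criteria) has a column of withdrawal criteria beside the inclusion and exclusion criteria. Several can be met only during or after the operation under comparison:

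- "Treatment implemented is proven to violate the study protocol";
- treatment outside the protocol during the treatment period, with treatment of recurrence and metastasis exempt;
- adjacent-organ invasion needing combined resection, or distant metastasis, found at operation or by pathology;
- inability to complete the trial, with no limit on the reason.

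The column also holds eligibility failures shown by final pathology (not colorectal adenocarcinoma; multiple malignant lesions). The table does not say which items end protocol treatment, which end follow-up and which remove a patient from analysis.

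Three other sections bear on the consequence. Statistical methods runs the primary noninferiority comparison "on a modified intent-to-treat (MITT) population basis", adds a per-protocol analysis, and lets the modified intention-to-treat result prevail. Primary endpoint dates patients without an event to their latest visit or examination. Randomization and blinding makes the trial open to patients and investigators. Sample size calculation allows for losses: "Considering that the largest abscission rate in this clinical study is approximately 20" per cent.

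**The concern.** Some of these criteria describe what happens to a patient once the allocated operation has begun, so the frequency of withdrawal, and the prognosis of those withdrawn, may differ by arm. The Discussion itself describes single-incision surgery as technically more demanding.

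Withdrawal can reach the primary result by two routes. First, a modified intention-to-treat set leaves out some randomised patients, and Table 2 is the only printed list of grounds on which that could happen. Second, even if the set keeps everyone, a patient whose follow-up ends at withdrawal soon after surgery is censored near time zero. In a Kaplan–Meier estimate that is nearly the same as exclusion, and the censoring may be informative.

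In a noninferiority trial, losing poor-prognosis patients from the experimental arm favours the study hypothesis. A per-protocol analysis in its usual sense would not correct this, because it drops protocol violators too. The 20% allowance protects the number analysed; it does nothing about who is lost.

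**Working it through.** **Inputs from the article (Sample size calculation).** Control DFS: "the 3-year DFS of the CLS group was approximately 75" per cent. Planning assumption: "This study assumes that the 3-year DFS of the study group is the same as that of the control group". Margin: "If the acceptable noninferiority limit of DFS in the three years of this study is 10" per cent. One-sided level 0.025, power 80%, 3 years of accrual plus 3 years of follow-up, HR limit 1.49, 284 per group, raised to 355.

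**The plan's own figure.** Take exponential DFS, Schoenfeld's formula and uniform accrual.

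- Hazard = −ln(0.75)/3 = 0.0959 per year.
- HR limit = ln(0.65)/ln(0.75) = 1.497 (stated as 1.49).
- Events = 4 × (1.960 + 0.842)² / (ln 1.49)² = 197.4, so 198.
- Event probability = 1 − (e^(−3×0.0959) − e^(−6×0.0959))/(3×0.0959) = 0.348.
- Per group = 197.4/0.348/2 = 283.5, so 284. With the loss allowance, 284/0.80 = 355.

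Both figures reproduce, so the point does not touch the sample size. The allowance tolerates 355 − 284 = 71 losses per group.

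**Illustration. These assumptions are not in the documents.** True 3-year DFS is 75% in the conventional arm and 65% in the single-incision arm, exactly at the margin. A net excess share w of single-incision patients is lost from the primary analysis, with 3-year DFS s. The test asks whether the lower limit of the two-sided 95% interval for the rate difference lies above −10 points. The range of n is 284 to 355 per arm before withdrawal.

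- DFS among those remaining: p = (0.65 − w·s)/(1 − w).
- Observed deficit: d = 0.75 − p.
- SE = √[p(1 − p)/(n(1 − w)) + 0.75×0.25/n].
- False noninferiority rate = Φ((0.10 − d)/SE − 1.96).

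Worked case, w = 0.05, s = 0.30, n = 355 (about 18 patients): p = (0.65 − 0.015)/0.95 = 0.668; d = 0.0816; SE = 0.0344; (0.10 − 0.0816)/0.0344 = 0.535; Φ(0.535 − 1.96) = 7.7%. With n = 284 the result is 6.9%.

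| Excess withdrawal w | DFS in those withdrawn s | DFS among those remaining | False noninferiority rate, n = 284 to 355 |
|---|---|---|---|
| 0 | – | 65.0% | 2.5% |
| 3% | 30% | 66.1% | 4.7–5.0% |
| 5% | 40% | 66.3% | 5.3–5.7% |
| 5% | 30% | 66.8% | 6.9–7.7% |
| 5% | 20% | 67.4% | 9.0–10.2% |
| 8% | 30% | 68.0% | 12.1–14.0% |
| 5% | 65% (arm average) | 65.0% | 2.5% |

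**When there is no inflation.** The last row shows that loss of average-risk patients leaves the rate at 2.5%. Equal loss in both arms also does no harm in this direction: with 5% lost in each arm at 30% DFS, the rates are 0.735/0.95 = 77.4% and 0.635/0.95 = 66.8%, a deficit of 10.5 points, which is slightly conservative. The bias needs loss that is both prognostic and unequal between arms.

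**The case against.** The strongest reply is that no sentence in the article says withdrawn patients leave the primary set. The article condenses version 1.1 of the full protocol, which is not shown, nor is an analysis plan; the definition of the modified set commonly sits there. A separate per-protocol analysis also suggests that violators remain in the modified set. This stands as far as it goes: a reader might infer that Table 2 withdrawals are excluded from the primary analysis, and the documents do not establish it. It does not dispose of the point, because the withdrawal rule is printed, and a set definition alone would not stop follow-up ending at withdrawal and the patient being censored there.

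Four further inferences are tempting and unsupported:

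- *That the criteria are events which surgery causes.* One item reads "Requirement of emergency operation due to the change of illness state". It concerns a change in the patient's condition, sits beside inability to undergo surgery or anaesthesia, and may well refer to the interval of up to 7 days between enrolment and operation. Invasion or metastasis is found at surgery, not caused by it.
- *That a positive margin or inadequate dissection means withdrawal.* Interventions says "Radical resection (R0) based on the same oncological principles is required for all operations", but nothing makes missing that standard a ground for withdrawal. Margins, nodes harvested and mesenteric integrity are secondary outcomes, so the protocol expects to measure them in trial patients.
- *That conversion is a violation.* Interventions provides for conversion, and the conversion rate is an outcome.
- *That unblinded surgeons decide on withdrawal.* The trial is open-label, but the article does not say who decides, and the violation item requires proof.

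The exemption for treatment of recurrence and metastasis also means that treating a DFS event does not trigger withdrawal under the off-protocol item.

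**Conclusion.** The point holds in limited form. The article prints withdrawal criteria that are met after randomisation, some of which may depend on the operation, and one of which is open-ended. It combines them with a prevailing modified intention-to-treat set and censoring at last contact, and says nothing to keep withdrawn patients in follow-up. Applied as written, the rule leaves room for selective exclusion or early censoring, which would favour noninferiority.

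The documents do not show that this will happen or how often. The figure of about 7–8% against 2.5% rests on three assumptions: a true deficit exactly at the margin, 5% net excess loss in the single-incision arm, and 30% DFS in those lost. Across the assumptions tabulated the rate runs from 2.5% to 14.0%. This should be fixed before outcomes are known; it is not a demonstrated error in the primary result.

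**What to change.** 1. Divide the withdrawal column of Table 2 into items that stop protocol treatment and items that exclude from analysis. State that stopping protocol treatment does not stop follow-up.
2. Follow every randomised patient for DFS unless consent to follow-up itself is withdrawn, and analyse in the allocated arm regardless of protocol violation, conversion or other treatment.
3. Limit exclusions from the primary set to facts that the operation cannot influence (final pathology not colorectal adenocarcinoma; multiple primaries), judged blind to arm.
4. For adjacent-organ invasion or metastasis found at surgery, state the place of these patients in the primary set and add an all-randomised sensitivity analysis that retains them. Give a rule for their DFS, since a patient with metastasis at operation was not disease-free at the start of the clock.
5. Replace the open-ended inability-to-complete item with recorded reasons, and report withdrawals by reason and arm.

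The cost is wording in the protocol and analysis plan, blinded review of a few pathology reports, and some extra follow-up for patients who would otherwise have stopped. The DFS estimate may be less favourable. The planned 284 and 355 per group need not change on this account.
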